### Population

2.2.

This study aims to include *n *= 160 people with PTSD (part A), half of whom participate in the entire study (*n = *80 for part B). In addition, *n *= 30 control group participants are recruited (part A). All participants must be aged 18–64 years old. Exclusion criteria for both groups are listed in Table 1. More details on criteria assessed during the screening visit and amendments during the trial are listed in the Supplementary Material (S1 and S2). Power calculations are also described in the Supplementary Material (S3).

**Table 1. T0001:** Exclusion criteria.

Group	Exclusion criteria
PTSD	General exclusion criteria:
	- Current psychotic or manic episode
	- Benzodiazepine medication: Daily intake of benzodiazepines, or otherwise irregular intake of benzodiazepines (‘when needed’) but unable to withhold intake according to study procedures Exception: low evening doses (sleep medication)
	- For part B only: MRI contraindications
	Criteria assessed during screening session:
	- Does not receive a classification of current PTSD according to clinical interview assessment
Control	General exclusion criteria:
	- Current or past psychiatric disorder
	- Use of psychotropic medication
	- History of childhood maltreatment
	Criteria assessed during screening session:
	- Early-life adversity according to questionnaire assessment
	- (History of) psychiatric disorders according to clinical interview assessment
Both	General exclusion criteria:
	- General learning disability or intellectual disability
	- Body mass index > 35 kg/m^2^
	- Pregnancy or breastfeeding
	- Substance use: Unable or unwilling to withhold recreational drug use and limit alcohol use according to study procedures
	- Nicotine smoking: Unable or unwilling to discuss frequency and timing of smoking according to study procedures
	- Glucocorticoid medication/supplements: Current or recent regular use of systemic corticosteroids (< 1 month ago). For non-systemic corticosteroids, average use of more than once a week and/or no possibility to withhold according to study procedures
	- Hypersensitivity to glucocorticoids
	Criteria only if relevant to study outcomes or feasibility of study procedures:
	- Relevant neurological disorder
	- Severe physical disorder
	- Relevant endocrine disease and/or current or recent endocrine treatment

Note: MRI = magnetic resonance imaging; PTSD = post-traumatic stress disorder; BMI = body mass index.

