#### Pharmacological intervention and fMRI study (Part B)

2.5.5.

Owing to the crossover design, this study part consists of two sessions that are scheduled with a 4–6 week interval. The sessions are identical, except for the type of drug administered (hydrocortisone or placebo) and the version of the fear conditioning and extinction task (different VE with different set of CSs). Each session includes two visits to the Donders Centre for Cognitive Neuroimaging on subsequent days (Figure 3). Before each visit, participants receive instructions for quality assurance of data (for details, see Supplementary Material S6).

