##### Primary outcome measures

2.6.2.1.

Successful fear acquisition, as indicated by a higher SER for the CS+s in comparison to CS− in the last block of the fear acquisition task, is a prerequisite for the assessment of extinction learning. During the fear extinction task, fear extinction should be indicated by decreasing SER, showing no expectancy of shock in the last block of this task. Fear acquisition and fear extinction will also be signalled by psychophysiological outcome measures (SCR and PDR). Neuroimaging during the fear extinction task investigates pharmacological effects on neural responses associated with fear extinction learning. Ultimately, the strength and generalization of the fear and extinction memories are assessed in the extinction recall task during recall of these memories upon presentation of the CSs in different contexts. Here, the primary outcome variables are SCR, PDR, and SER. Details of psychophysiological analyses are described in Supplementary Material S13. More specifically, increased strength of extinction memory should be indicated by smaller differential responses within the extinction context, whereas increased generalization of extinction memory should be indicated by a context interaction effect showing transfer of extinction to novel and/or acquisition contexts. In addition, effects of HPA-axis dysregulation are investigated to investigate their role in glucocorticoid effects on extinction recall. Relative suppression of the CAR from the DST is prespecified as the primary outcome measure, and based on a median split, the PTSD group will be divided over two subgroups. Grouping based on other HPA-axis outcome variables will be regarded as secondary and subjected to appropriate multiple-comparison corrections. Planned MRI (preprocessing) analyses are discussed in the Supplementary Material (S14).

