##### Statistical modelling

2.6.2.2.

1. Investigate whether patients with HPA-axis dysregulation show impairments in extinction learning relative to patients without HPA-axis dysregulation, and whether this is accompanied by different neural responses during extinction learning in brain regions associated with fear expression and extinction.

This objective will be investigated with data from placebo sessions only. At the psychophysiological level, we expect HPA-axis dysregulation to be associated with lower strength of the extinction memory, indicated by lower differential responses for CS+U vs CS+E and/or higher differential responses for CS+E vs CS− during the extinction recall task. This will be modelled with a two-way ANOVA of averaged differential responses during the first block, which is within the extinction context and contains two presentations of each CS. Higher generalization of the extinction memory for the HPA-axis normalized group would be indicated by a context interaction effect that shows less renewal of fear, i.e. a lower increase of differential effects upon stimulus presentations within the novel and acquisition contexts. These comparisons may be affected by an overall attenuation of fear responses due to re-extinction over the course of the extinction recall task. This effect will be investigated with a 2 (group) by 3 (context) mixed ANOVA of averaged differential responses during the first block of each context. Both models will include the covariate order of medication administration, and, if appropriate, the covariates age and gender. Outcome measures SCR, PDR, and SER will be included in separate models, but since these measures of conditioning are complementary, no multiple comparisons correction will be applied. At the level of neuroimaging, differences in extinction learning signalled during the fear extinction task could be underlying the differences at the behavioural level. Here, we would expect different neural responses in brain regions and networks associated with (context-dependent) extinction learning for patients with HPA-axis dysregulation, which could also be associated with less successful recall of the extinction memory.

2. Investigate whether the subgroup of PTSD patients with HPA-axis dysregulation particularly benefits from hydrocortisone administration (versus placebo) to improve the strength and generalization of extinction memories.

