To answer the main objective of the pharmacological intervention study, the aforementioned psychophysiological models will be extended with data from the hydrocortisone sessions (thus adding a within-subjects category for medication). Period effects may follow from the crossover design and will be accounted for by defining a medication-by-order interaction effect. Based on previous research, we hypothesize a group-by-medication interaction effect, indicating greater strength and/or generalization of the extinction memory following administration of hydrocortisone, that is most pronounced for the HPA-axis dysregulation group.

3. Investigate underlying neural mechanisms of glucocorticoid administration (versus placebo) to improve extinction learning.

Recruitment of neural networks associated with (context-dependent) extinction learning for patients with HPA-axis dysregulation (see point 1 above) would be expected to enhance following hydrocortisone administration. Pharmacological effects and their potential interactions with HPA-axis dysregulation are primarily investigated during the extinction learning task, but will also be supported by the following analyses: (1) amygdala (and salience network) reactivity to the emotion processing task, which we expect to be reduced after hydrocortisone administration; and (2) resting-state connectivity in networks associated with (context-dependent) extinction learning – ventromedial prefrontal cortex–amygdala connectivity, in particular – which we expect to be enhanced after hydrocortisone administration.

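### The recall ANOVAs for the hydrocortisone objective cannot use partly observed patients; the loss is small for strength and moderate for generalization, and a mixed model would recover much of it

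*Protocol article*

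**What the plan says.** All references are to the protocol article.

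- **Design.** Section 2.2 plans 160 people with PTSD, "half of whom participate in the entire study", so 80 in part B. Section 2.5.5 states that "this study part consists of two sessions that are scheduled with a 4–6 week interval".
- **Recall task.** Section 2.4.5.1 gives six blocks, two in each of three contexts, with two presentations of each stimulus per block.
- **Strength model.** Section 2.6.2.2, objective 1, names a "two-way ANOVA of averaged differential responses during the first block", which lies in the extinction context.
- **Generalization model.** The same section names a "2 (group) by 3 (context) mixed ANOVA of averaged differential responses during the first block of each context".
- **Hydrocortisone test.** Under objective 2, "the aforementioned psychophysiological models will be extended with data from the hydrocortisone sessions (thus adding a within-subjects category for medication". Period effects are handled through a medication-by-order interaction, and "we hypothesize a group-by-medication interaction effect".
- **Groups.** Section 2.6.2.1 forms the HPA groups on suppression of the cortisol awakening response: "based on a median split, the PTSD group will be divided over two subgroups".
- **Outcomes.** Skin conductance, pupil dilation and shock expectancy are analysed in separate models.

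The article does not say how a missing session or an unusable block is treated. It refers to supplements that are not shown for power (S3), for adapting the analyses if the sample size is missed (S12) and for psychophysiological analysis (S13).

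**The concern.** The article leaves missing-data detail to other documents, which is normal, but it does fix the model. A repeated-measures ANOVA on cell averages, fitted classically, takes a patient only if every within-subject cell is filled.

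Incomplete patients are foreseeable. Each session includes shocks and scanning, the second follows weeks after the first, and section 2.5.8 provides for people who discontinue. Each analysed cell rests on two presentations per stimulus, so a little artefact can make it unusable.

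Two things are at stake:

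- **Precision.** Responses already collected from partly observed patients are not used in the main test. By March 2024 only 19 patients had completed part B (section 3.1), so each one matters.
- **Validity.** A complete-case contrast is safe only if missingness is unrelated to response. A likelihood-based mixed model is also valid when missingness depends on responses that were observed, for example in session 1.

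**Working it through.** **The plan's own figure.** The total of 80 cannot be reproduced. "Power calculations are also described in the Supplementary Material (S3", which is not shown, and the article gives no alpha, power, effect size, SD or dropout allowance.

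**Inputs from the article.** N = 80; two sessions; one analysed block per context; one context for strength and three for generalization.

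**Inputs assumed.** Withdrawal after session 1, d = 10% (range 0–20%); share of analysed cells unusable, p = 3–5% (range 0–10%), independent between cells; variance components of 0.3 (patient), 0.1 (patient-by-session) and 0.6 (residual).

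**Step 1: cells needed per patient and outcome.** Strength: 1 × 2 sessions = 2. Generalization: 3 × 2 sessions = 6. The second block of each context is not analysed, so losing it costs nothing.

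**Step 2: patients kept by the ANOVA** = 80 × (1 − d) × (1 − p)^cells.

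- Strength, d = 10%: 72 × 0.97² = 67.7; 72 × 0.95² = 65.0.
- Generalization, d = 10%: 72 × 0.97⁶ = 60.0; 72 × 0.95⁶ = 52.9.

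Across the wider range:

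| d | p | Strength | Generalization |
|---|---|---|---|
| 0 | 2% | 76.8 | 70.9 |
| 0 | 5% | 72.2 | 58.8 |
| 10% | 0 | 72.0 | 72.0 |
| 10% | 10% | 58.3 | 38.3 |
| 20% | 5% | 57.8 | 47.0 |

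**Step 3: variance of the complete-case contrast divided by that of a mixed model on the same data** (generalized least squares with known covariance, 400 simulated missingness patterns).

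| Scenario | Strength | Generalization |
|---|---|---|
| d = 10%, p = 3% | about 1.07 | about 1.2 |
| d = 10%, p = 5% | about 1.08 | about 1.36 |
| d = 10–15%, p = 0 | 1.04–1.06 | 1.03–1.09 |

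The generalization column covers both the group-by-medication contrast and its interaction with context. Repeat simulation moves the entries by about 0.01.

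**Step 4: other correlations.** The results are expressed as effective patients out of 80.

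- Strength, withdrawal only, between-session correlation from 0.7 down to 0.2: at 10%, 72 complete cases against 73.2–75.2 under a mixed model; at 20%, 64 against 66.4–70.4.
- Generalization, correlations 0.3 between and 0.5 within sessions: at p = 5% and no withdrawal, 58.6 against 74.8; at p = 5% and d = 10%, 52.4 against 70.9 (70.9/52.4 = 1.35); at p = 10% and d = 10%, 37.7 against 65.8.

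**Step 5: power benchmark.** Treat the interaction as a two-sample comparison of within-patient contrasts, two-sided 0.05. With 40 per group, the effect detectable at 80% power is (1.960 + 0.842) × √(2/40) = 0.626 SD. At that effect, with d = 10% and p = 5%, power is 71.4% with 65 patients (strength) and 62.5% with 53 (generalization). These fall short of 80% by more than a mixed model could recover, because data that were never observed are lost under either method.

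**The case against.** The strongest reply is that the article never says incomplete patients are dropped. It names a factor and a family of models; the rule for missing sessions and unusable blocks may sit in S12, S13 or an analysis plan that is not shown. This stands as a limit: exclusion is what the named method does when fitted in the usual way, not a stated rule. It does not remove the point, because the choice of model is in the article and a better one is available for the same data.

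Four stronger readings are tempting, and the documents do not support them:

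- **Any lost block removes the patient altogether.** Only the first block of each context is analysed. A lost novel- or acquisition-context block cannot affect strength. Because the outcomes are modelled separately, a pupil artefact leaves the skin conductance and expectancy tests intact.
- **Stopping after session 1 is the costly case.** The target is mainly a within-patient contrast, to which one session adds little; withdrawal alone costs a few per cent.
- **The result is biased.** Nothing in the article shows that withdrawal depends on fear, drug or HPA group. The advantage of the mixed model is protection if it does.
- **Objectives 1 and 2 conflict because they can rest on different patients.** Objective 1 uses placebo sessions only, so this follows from its definition and is not an inconsistency.

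It is also fair that every rate is assumed. If unusable cells cluster within patients, fewer patients are lost than the independence formula gives, and a mixed model recovers less.

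**Conclusion.** The concern holds in limited form. The named ANOVAs do not use partial data, and a mixed model on the same responses does. The gain lies mainly in isolated missing cells of the six-cell generalization model, where the ANOVA's variance is about 1.2–1.4 times larger at 10% withdrawal and 3–5% unusable cells. For strength it is about 1.07–1.08 times larger, and for withdrawal of 10–15% alone about 3–9% larger. These sizes rest on assumed rates, independent cell loss and assumed variance components. The further benefit, validity when missingness depends on observed responses, cannot be sized from the article. The change is worth making because it is cheap; it is not a flaw that invalidates the trial.

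**What to change.** In section 2.6.2.2, objectives 1 and 2, replace the ANOVAs with linear mixed-effects models (REML) fitted to all available first-block recall responses:

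- Fixed effects: group, medication, context and their interactions, plus period, as each objective requires. The covariates already named can stay.
- Random effects: patient, plus patient-by-session where context is modelled. Where a model has only one value per patient (strength under objective 1), it reduces to an ordinary linear model and nothing changes.
- Analysis set: every participant with at least one usable recall response for that outcome.
- Reporting: withdrawals between sessions, by drug received first and by HPA group.

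The cost is a change of analysis wording and slightly more programming, with no new data; section 2.6.1.2 already names mixed-effects regression for part A objective 4. The model relies on a missing-at-random assumption, which should be stated.

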### Pharmacological intervention

2.3.

In part B of the study, to investigate glucocorticoid effects on extinction learning and brain activity, participants ingest 20 mg hydrocortisone prior to extinction learning in one session, and placebo prior to extinction learning in the other session. The order of medication administration is double-blind and counterbalanced across participants (for details see Supplementary Material S4).

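### The objective 2 crossover model crosses only order with medication; age and gender, if entered as main effects alone, cannot adjust the group-by-medication test on the non-randomised HPA split

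*Protocol article*

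**What the plan says.** All references are to the protocol article.

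- **Covariates, section 2.6.2.2, objective 1 (placebo sessions only).** "Both models will include the covariate order of medication administration, and, if appropriate, the covariates age and gender". Order is always in; age and gender are conditional. The generalization model is specified so: "This effect will be investigated with a 2 (group) by 3 (context) mixed ANOVA of averaged differential responses".
- **Extension, section 2.6.2.2, objective 2.** "the aforementioned psychophysiological models will be extended with data from the hydrocortisone sessions (thus adding a within-subjects category for medication"). The one covariate-by-medication term named is for order: "Period effects may follow from the crossover design and will be accounted for by defining a medication-by-order interaction effect". Nothing is said about age or gender by medication.
- **Test of main interest, same section.** "we hypothesize a group-by-medication interaction effect".
- **Grouping, section 2.6.2.1.** HPA status is defined by relative suppression of the cortisol awakening response, and "based on a median split, the PTSD group will be divided over two subgroups".
- **What is allocated by design, section 2.3.** "The order of medication administration is double-blind and counterbalanced across participants". HPA group is not allocated.
- **Size, section 2.2.** Part B has 80 patients, from a PTSD group of 160, "half of whom participate in the entire study".

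**The concern.** Order, age and gender stand in one covariate sentence for objective 1. When medication is added for objective 2, only order is given an interaction with it. The natural reading, though not an explicit statement, is that age and gender stay as main effects.

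In a crossover such a term does nothing for the test of interest. Age and gender do not change between a patient's two sessions, so their main effects drop out of the hydrocortisone-minus-placebo difference, and the group-by-medication estimate is the same with or without them.

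This matters because counterbalancing of medication order protects the medication comparison but not the comparison of drug response between two observed groups. The article itself treats age and gender as relevant to HPA measures: they are covariates in the part A HPA models (section 2.6.1.2), and hormonal contraceptive use is mentioned as a possible confounder (section 2.2.1). If one HPA group held more women and hydrocortisone worked differently in women and men, that difference could be credited to HPA-axis dysregulation.

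**Working it through.** The article gives no figure on this point and leaves the power inputs to its Supplement S3, so there is nothing to reproduce. The check is algebraic, followed by an illustration under stated assumptions.

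**1. Algebra.** For patient *i*, with medication *m* = 0 (placebo) or 1 (hydrocortisone), HPA group *g*, order *o* and a patient-level covariate *x*:

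y_i(m) = u_i + γx_i + m(δ + βg_i + θo_i + λx_i) + e_i(m) + period effect.

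Subtracting placebo from hydrocortisone, with the period effect absorbed by the order term:

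d_i = δ + βg_i + θo_i + λx_i + error.

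The main effect γx_i has gone. Any confounding through it has gone too, which is to the design's credit. The term λx_i remains only if *x* modifies the drug effect. If it is left out of the model, and order is balanced over groups, the estimate of β is centred on

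β + λ × (mean of *x* in group 1 − mean of *x* in group 0).

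Bias therefore needs λ ≠ 0 **and** a group difference in *x*.

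**2. Numerical confirmation.** One simulated crossover: 80 patients, 40 per HPA group, balanced order, random-intercept mixed model. The 40/40 split assumes that the median is taken among the part B patients.

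| Model | group-by-medication | SE |
|---|---|---|
| group × med + order × med | −0.01866 | 0.2125 |
| same + age + gender main effects | −0.01866 | 0.2125 |
| same, age and gender crossed with med | −0.02326 | 0.2014 |

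The first two equal the unadjusted analysis of within-patient differences; the third equals that analysis adjusted for age and gender.

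**3. Illustrative size.** 4,000 simulations per scenario, true group-by-medication effect 0, SD of the within-patient difference 1, two-sided 5%. The shares of women and the gender-by-drug effects are assumptions. The unequal shares average 57.5% or 60% women over equal groups, inside the 40–75% range that section 2.2.1 accepts. Expected bias is gap × effect.

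| Women, group 1 v 0 | Gender-by-drug effect (SD) | Expected bias | Simulated bias | Rejection, main effects only | Rejection, crossed |
|---|---|---|---|---|---|
| 65% v 50% | 0.3 | 0.15 × 0.3 = 0.045 | 0.047 | 5.6% | 4.8% |
| 65% v 50% | 0.5 | 0.075 | 0.073 | 6.0% | 5.1% |
| 65% v 50% | 0.8 | 0.120 | 0.128 | 8.1% | 4.5% |
| 75% v 45% | 0.3 | 0.090 | 0.081 | 6.4% | 5.2% |
| 75% v 45% | 0.5 | 0.150 | 0.145 | 9.7% | 5.0% |
| 75% v 45% | 0.8 | 0.240 | 0.239 | 16.2% | 4.5% |
| 75% v 40% | 0.3 | 0.105 | 0.104 | 7.7% | 4.6% |
| 75% v 40% | 0.5 | 0.175 | 0.170 | 11.1% | 5.3% |
| 75% v 40% | 0.8 | 0.280 | 0.278 | 20.5% | 4.6% |

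With equal shares of women, or with no gender-by-drug effect, the main-effects model rejected in 4.3% to 5.7% of simulations. With the crossed terms, rejection over all scenarios was 4.5% to 5.9% and absolute bias at most 0.007 SD.

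**4. Objective 1.** The strength model has one placebo value per patient, so main effects do adjust its group comparison. The group-by-context test is a within-patient contrast, and the cancellation in step 1 applies to it with context in place of medication.

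**The case against.** **The text does not exclude the missing terms.** Medication-by-order is named for one purpose, period effects, and naming it does not rule out others. A classical mixed or repeated-measures ANCOVA commonly crosses every between-subject term with the within-subject factors, and the test would then be adjusted. This stands: a reader might infer that the plan fixes age and gender as main effects only, but the article does not say so. What remains is that the two readings give different tests, and that the text spells out the interaction for one covariate and not for the other two.

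**This is analysis-plan detail.** The article is condensed, and its supplement and any SAP are not shown. Centring and coding are indeed such detail. But the article does specify the model and a covariate interaction for the main objective of part B, and that specification, on its natural reading, leaves the key test unadjusted.

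**The harm is hypothetical.** It needs both an imbalance and effect modification, and the documents show neither. That stands too. A reader might also infer that the result will be presented as age- and gender-adjusted; no section says so, and inclusion is itself conditional.

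**Unadjusted moderation is a legitimate target.** If HPA status is to serve as a biomarker (section 4), whether the subgroup responds better is a fair question without adjustment. This is a reason to report both estimates. Nor would adjusting for two covariates make the grouping causal.

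**Conclusion.** The point holds as a matter of specification. On the natural reading of section 2.6.2.2, age and gender cannot adjust the group-by-medication test even when they are included, and the HPA grouping has no protection from randomisation. The cancellation is exact and rests on no assumption beyond main effects only.

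The consequence is conditional. Under the assumed range of imbalance and effect modification, the false-positive rate runs from about 6% to about 20% in place of 5%; the upper end needs a 35-point gender gap together with a 0.8 SD gender-by-drug effect. If either is absent, the error rate is nominal. The documents do not support saying that the planned test is confounded, only that the model as described would not remove such confounding if it were present.

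**What to change.** State in section 2.6.2.2, or in the analysis plan, that age (mean-centred) and gender (effect-coded), when included, are crossed with:

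- medication in the objective 2 strength model;
- medication, context and medication-by-context in the objective 2 generalization model;
- context in the objective 1 group-by-context model.

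Centring and effect-coding keep the medication main effect interpretable at average age and across genders. The unadjusted group-by-medication estimate can be reported alongside.

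**Cost.** One sentence. In the strength model, about two degrees of freedom: the analysis of differences goes from 80 − 3 = 77 to 80 − 5 = 75 residual degrees of freedom, with one more lost if gender has a third category. In the context models, with three contexts, the crossed terms number 1 + 2 + 2 = 5 per covariate for objective 2 and 2 per covariate for objective 1. In the simulated example the SE fell, from 0.2125 to 0.2014. No new data are needed. By March 2024, 19 of the planned 80 patients had completed part B (section 3.1).
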